##### Young Children’s Participation and Environment Measure (YC-PEM)

The YC-PEM, aimed to be used for children from zero to five years, explores the frequency of participation in activities, the level of involvement of participation, the parent’s satisfaction with the children’s current participation and the environmental supports and barriers considered to be important. Parents will report their child’s participation across home, community and childcare activities. For each type of activity, parents will report on (1) frequency of attendance (i.e., how often the child attends an activity) (8-point scale, from never (0) to once or more times every day (7); (2) level of involvement (i.e., the child’s level of engagement in the activity) (5-point scale, from not very involved (1) to very involved (5)); and (3) their desire for their child’s participation to change (i.e., their dissatisfaction) [yes, no]. Then, caregivers will evaluate the impact of environmental features and resources on participation (3-point scale, from usually helps/usually yes (3) to usually makes harder/usually no (1)). The YC-PEM will be administered at baseline and at the end of the 12th week of the intervention [34].

##### Goal Attainment Scaling (GAS)

GAS is an objective method of quantifying goal attainment. Goals are scored on a Likert-type scale from −2 (representing no positive change at all from baseline/ regression), −1 (a little less change than expected), 0 (attainment of goal at the expected level), +1 (a little more change than expected), to +2 (attainment of goal at much more than the expected level) [35]. Goals are personally relevant to the individual family (rather than standardized), with the distance between each increment representing a relatively equal amount of effort or improvement to achieve. Outcome scores on an individual’s goals will be converted to an aggregate T score (regardless of the domain to which the GAS goal is aligned) which will be the unit of analysis. One to three GAS goals will be set in the baseline and at the end of the 8th week of the intervention. At the end of the 12th week of the intervention, the goals will be reviewed.

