### 2.3. Sample Size Estimation

In this feasibility study, we will recruit 10 children with CZS. This small sample will provide data on the feasibility of the protocol, thus helping determine the sample size for a larger randomized trial using powered mobility in children with CZS. Given the lack of previous studies measuring the outcomes of interest for this study, the sample size was estimated according to recommendations of the minimum sample for pilot studies [22].

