### 2.9. Statistical Analysis 

Quantitative data will be imported into the Statistical Package for Social Science (SPSS) 22.0 for analysis and reported using descriptive statistics (absolute and relative frequencies, measures of central tendency and measures of variability). For numerical data, the Wilcoxon test will be used when there are two measurements, while the Friedman test will be used when there are more than two measurements. For categorical data, the Chi-Square test will be used. All the analyses will consider a confidence interval of 95% (CI95%) and a statistical significance of p < 0.05. Adverse events will be categorized. The percentage of scheduled and completed treatment sessions will be compared.

The feasibility results will be presented qualitatively. The researchers will analyze the audio transcripts of the focus group, Photovoice and additional questions through the thematic analysis to identify and validate the significant themes and patterns from the discussion with the parents. The ATLAS.ti software will be used to code, group and present the data, based on the results.

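### The general test rule, if applied to GAS, compares the T score with a fixed floor, and goals set at baseline and at week 8 share one score

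*Protocol article*

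**What the plan says.** The GAS part of section 2.6.2 uses a five-level scale from −2 to +2. The lowest level is described as "representing no positive change at all from baseline/ regression", and level 0 as "attainment of goal at the expected level". Each child's goal scores are "converted to an aggregate T score (regardless of the domain to which the GAS goal is aligned) which will be the unit of analysis".

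On timing it states "One to three GAS goals will be set in the baseline and at the end of the 8th week of the intervention", and then "At the end of the 12th week of the intervention, the goals will be reviewed". It does not say whether the week-8 goals replace, revise or add to the baseline goals, or which of them enter the T score.

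Table 1 marks GAS at baseline, week 8 and week 12. Section 2.9 gives a general rule: "For numerical data, the Wilcoxon test will be used when there are two measurements", with the Friedman test for more than two, at a 0.05 significance level. It does not name GAS. Section 2.3 plans a single group: "In this feasibility study, we will recruit 10 children with CZS".

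**The concern.** There are two separate problems.

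**The comparator.** On this scale, a child who has not moved scores −2 and a child who has got worse also scores −2. Baseline status is therefore a constant and not a measurement with variation. If the T score at later visits is tested against baseline, every non-zero difference on the same goals is positive. A small p-value then shows only that several children moved off the floor. It does not show that they reached the level their families set as the target.

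**The mixture.** Goals set at baseline have 12 weeks to run by the final review, and goals set at week 8 have four. One T score over both sets has no clear meaning, and its value depends on how many goals were added.

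The second specific aim in the Introduction is to determine the effect on mobility, social function and participation. Section 2.7 directs the sessions at the caregivers' GAS goals, and there is no control group. Section 2.11 plans a policy brief. A significant rise from the floor could be read there as evidence of effectiveness.

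**Working it through.** The plan gives no GAS effect size, power or T-score figure to reproduce. Section 2.3 says only that "the sample size was estimated according to recommendations of the minimum sample for pilot studies".

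**Inputs from the article:** n = 10; baseline level −2; expected level 0; one to three goals per setting occasion; significance level 0.05.

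**Assumptions not in the article:** the usual T formula with equal weights and inter-goal correlation ρ = 0.3 (0 and 0.5 also shown); two-sided tests; no dropout; the chance q that a child leaves −2 on at least one goal; independent goals where a per-goal chance is used.

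**1. The floor.** For k goals with scores x, T = 50 + 10·Σx / √((1 − ρ)k + ρk²).

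| Goals k | Denominator, ρ = 0.3 | T, all at −2 | T, all at −1 | Rise |
|---|---|---|---|---|
| 1 | √1.0 = 1.000 | 30.0 | 40.0 | 10.0 |
| 2 | √2.6 = 1.612 | 25.2 | 37.6 | 12.4 |
| 3 | √4.8 = 2.191 | 22.6 | 36.3 | 13.7 |

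T can thus rise by 10 to 14 points while every goal is missed. At ρ = 0 and ρ = 0.5 the floor is 21.7 and 26.9 for two goals, and 15.4 and 25.5 for three.

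**2. What reaches p < 0.05.** If m children leave −2 and the rest stay, all m non-zero differences are positive, so the exact two-sided Wilcoxon p = 2 × (1/2)^m.

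- m = 5: 2/32 = 0.0625.
- m = 6: 2/64 = 0.031.

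The large-sample version needs five children (p = 0.043, no ties), or four if all gains are equal (p = 0.0455). A large-sample Friedman test over baseline, week 8 and week 12 reaches p = 0.0498 with three of ten children, whether they move by week 8 and hold or move only by week 12.

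**3. How often.** With the exact Wilcoxon test, the chance of significance is P(Bin(10, q) ≥ 6).

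| q | 0.3 | 0.5 | 0.6 | 0.7 | 0.8 |
|---|---|---|---|---|---|
| Chance | 5% | 38% | 63% | 85% | 97% |

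If p is the chance that a single goal leaves −2, then q = 1 − (1 − p)^k. For k = 1, 2, 3 goals:

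- p = 0.5: q = 0.500, 0.750, 0.875; chance 38%, 92%, 99.6%.
- p = 0.3: q = 0.300, 0.510, 0.657; chance 5%, 40%, 77%.

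**4. Significance with poor attainment.** Suppose each goal ends at −2, −1, 0 or +1 with chances 50%, 30%, 15% and 5%. Only 20% of goals reach the expected level. The mean goal score is −1.00 − 0.30 + 0 + 0.05 = −1.25, so mean T is 37.5, 34.5 and 32.9 for one, two and three goals. The test against the floor is still significant in 38%, 92% and 99.6% of trials (the p = 0.5 row above). In simulation, a test against T = 50 never indicated above-expected attainment in this case.

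**5. Pooling the two goal sets.** Three baseline goals all at 0 give T = 50. Adding three week-8 goals makes k = 6, with denominator √(0.7 × 6 + 0.3 × 36) = √15 = 3.873.

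- Week-8 goals at −2: 50 − 60/3.873 = 34.5.
- Week-8 goals at −1: 50 − 30/3.873 = 42.3.
- First case at other correlations: ρ = 0 gives 50 − 60/√6 = 25.5; ρ = 0.5 gives 50 − 60/√21 = 36.9.

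The number of goals alone also moves T: one goal at −2 gives 30.0, and six goals at −2 give 19.0, with no change in the child.

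**The case against.** The strongest reply is that no sentence tests GAS against baseline. Section 2.9 is a generic rule. Goals are set at baseline and week 8 and reviewed at week 12, no baseline T score is mentioned, and the baseline mark in Table 1 may only record goal setting. This stands, and the first part of the point is conditional for that reason. But the other readings do not settle the matter. If GAS is scored once, neither paired test in section 2.9 fits its declared unit of analysis. If week 8 is compared with week 12, the article does not say that the same goals underlie both scores.

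A reader might infer that a significant result is close to guaranteed. The documents do not support that. The frequency rests on assumed rates and is about 5% with one goal at a 30% chance. The introduction describes most of these children as having the most severe motor classification, so low rates are plausible.

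A reader might also infer that setting goals at week 8 inflates the result, because an unmet goal could be exchanged for an easier one. The text does not say that goals are replaced, and pooling new goals still at a low level reduces T. What is supported is a loss of meaning, not a bias towards success.

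It is also too strong to say that regression goes unscored: it is scored, but at the same level as no change. Starting at −2 is a disclosed choice of scale. Moving the start to −1 would give up a level of partial progress and is not needed here.

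Finally, an analysis plan or full protocol that is not shown may settle which goals and visits are compared. That limits how far the gap can be pressed, but the article itself fixes the single T score, the two goal-setting times and the general test rule.

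**Conclusion.** The concern holds in conditional form. By the article's own scale, baseline status is the floor. If the general rule in section 2.9 is applied to the GAS visits in Table 1, the test can move in only one direction on unchanged goals, and it can be significant while most children miss their expected level: six of ten leaving −2 is enough with the exact Wilcoxon test. The threshold follows from n = 10 and the scale. How often it is crossed does not, and ranges from about 5% to nearly 100% over the assumed rates.

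Separately, a T score that pools 12-week and 4-week goals cannot be interpreted. The drop from 50 to 34.5 illustrates the size and depends on equal weights, ρ = 0.3 and three goals in each set.

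GAS is a secondary outcome. The point bears on the aim about effect and leaves the primary feasibility result untouched.

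**What to change.** Amend the GAS part of section 2.6.2 and section 2.9 to state that:

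- the analysed GAS T score uses only the goals set at baseline, unchanged;
- it is summarised against T = 50 as a median with a 95% confidence interval, together with the number of children at or above 50;
- no significance test against baseline is made for GAS;
- goals set at week 8 are reported separately, with a statement of whether they add to or revise the earlier goals.

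The goal-setting form should record when each goal was set. No new data are needed. The result will look less favourable than a rise from the floor, and goals that families adopt at week 8 will not count in the main score.

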### 2.7. Intervention

Modified ride-on car training sessions will be conducted three times a week at the participants’ home or in the clinic, according to family preference. A therapist will guide the sessions at both locations. The intervention session will include the following: (1) environment setup (e.g., instructing families) (5 min); (2) natural play as a warm up activity (5 min); and (3) social training and mobility with modified ride-on cars (30 min). The focus of treatment sessions will be based on the social function goals and the expected mobility set by caregivers in the modified GAS after the pretest [36]. The 30-minute driving session will involve the participants learning cause–effect concepts by driving the modified ride-on car (i.e., pressing the switch for moving and releasing it for stopping). The dose of the intervention will be adjusted considering the opinion of the parents who participated in a previous interview and the results of a recent study, where the average time of interventions was 24 to 30 min [37]. The therapist and caregivers then will use verbal and physical cueing to encourage children to drive and explore the surrounding environment [17,38]. All sessions will be video- and audio-recorded. Figure 2 shows a modified ride-on car and a child with CZS.

### 2.8. Modified Ride-On Cars

Ride-on cars will be modified with a joystick for activation. Joystick control will allow omni-directional turning and proportional speed-control. The vast majority of research with modified ride-on cars has installed a large, easy-to-press, all-or-nothing activation switch that does not provide turning nor speed control. These steering and speed modifications will enhance the ability for young children with CZS to explore the environment and use the device within the home and community. Joystick activation ensures that children are provided with an opportunity to use an activation method that is consistent with future joystick-driven device options, such as motorized wheelchairs. Ride-on cars will be modified with optimal seating support using readily available, low-cost materials based on each child’s individual needs. Ride-on car models will be selected based on their design and structure to provide seating support. 

### 2.9. Statistical Analysis 

Quantitative data will be imported into the Statistical Package for Social Science (SPSS) 22.0 for analysis and reported using descriptive statistics (absolute and relative frequencies, measures of central tendency and measures of variability). For numerical data, the Wilcoxon test will be used when there are two measurements, while the Friedman test will be used when there are more than two measurements. For categorical data, the Chi-Square test will be used. All the analyses will consider a confidence interval of 95% (CI95%) and a statistical significance of p < 0.05. Adverse events will be categorized. The percentage of scheduled and completed treatment sessions will be compared.

The feasibility results will be presented qualitatively. The researchers will analyze the audio transcripts of the focus group, Photovoice and additional questions through the thematic analysis to identify and validate the significant themes and patterns from the discussion with the parents. The ATLAS.ti software will be used to code, group and present the data, based on the results.

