## 2. Materials and Methods

### 2.1. Design

This is a feasibility trial of a mixed-methods case series, prospectively registered, with 3-month intervention and 1-month follow-up. The follow-up will aim to assess preliminary learning retention and implications of modified ride-on car training sessions [16]. This prospective study will provide important information about the feasibility, assistive effectiveness, and rehabilitative effectiveness of the first intervention focusing on powered mobility for children with CZS in Brazil. The procedures and timeline of the study are included in Figure 1 and Table 1.

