Quantitative data will be collected from feasibility questionnaires for parents and professionals. The parents feasibility questionnaire (PFQ) [29,30] includes questions related to satisfaction with the intervention, the time of use at home and in the community, the usefulness of the ride-on car, the level of comfort related to the time of its use and the need for help from others during use. PFQ will be used at the end of week 4, 8, and 12 of the intervention, and at follow-up. The assessment of learning powered mobility (ALP) [31] will be used to measure the feasibility of the intervention. This tool is able to describe the learning process’ phase at the initial stages of using a powered mobility device. It also documents the child’s occupational performance, thus supporting the selection of learning strategies. Phases are scored from 1 (novice) to 8 (expert) to describe occupational performance while using a powered mobility device, considering five categories: understanding of tool use, level of attention, expressions and emotions, activity and movement, and interaction and communication [31,32]. In this study, the ALP will be applied at the end of weeks 4, 8, and 12 of the intervention, and at the follow-up. In addition, a sociodemographic questionnaire will be used for all participants at the baseline.

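### The four-visit Friedman test that 2.9 assigns to the ALP cannot separate retained from lost skill at week 16; add one paired week 12 to week 16 contrast

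*Protocol article*

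**What the plan says.** Section 2.9 fixes the test by the number of time points. For numerical data, "the Wilcoxon test will be used when there are two measurements", and "the Friedman test will be used when there are more than two measurements". Section 2.6.1 says that "the ALP will be applied at the end of weeks 4, 8, and 12 of the intervention, and at the follow-up"; Table 1 places the follow-up at week 16 and the training sessions in weeks 1 to 12. The ALP phase runs from 1 (novice) to 8 (expert). Read as a numerical score with four measurements, it falls under the Friedman rule. As worded, the Wilcoxon test is kept for outcomes measured twice (PEDI-CAT and YC-PEM).

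Section 2.1 gives the purpose of the last visit: "The follow-up will aim to assess preliminary learning retention". In Table 1 only the ALP, the PFQ and the driving journal have a week-16 entry. Of these, the ALP is the one that measures skill.

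Section 2.9 also says that quantitative data will be "reported using descriptive statistics (absolute and relative frequencies, measures of central tendency and measures of variability"), and that "All the analyses will consider a confidence interval of 95% (CI95%) and a statistical significance of p < 0.05". It names no contrast between week 12 and week 16.

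**The concern.** Retention is a directional question about two visits: is the level reached when the sessions end still there a month later? The Friedman test asks whether any of the four visits differs from any other. It puts the learning period (weeks 4 to 12) and the period after the scheduled sessions (weeks 12 to 16) into one p-value. A rise from week 4 to week 12 can make it significant whatever happens afterwards.

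The risk is one of interpretation. With p < 0.05 set for all analyses, a significant ALP result that includes the follow-up visit could be read as support for retained learning when it carries no such information.

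**Working it through.** **Inputs.** From the documents: 10 children ("In this feasibility study, we will recruit 10 children with CZS"), four ALP visits, scale 1 to 8, significance level 0.05. The sample size has no effect size, SD or power behind it ("the sample size was estimated according to recommendations of the minimum sample for pilot studies [22"), so there is no planned figure to reproduce. All means and SDs below are assumptions.

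**Step 1: the statistic ignores order.** For n children and k visits with rank sums R_j,

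χ² = [12 / (n·k·(k+1)) · ΣR_j² − 3n(k+1)] / C, where C = 1 − Σ(t³ − t) / (n·k·(k² − 1)) corrects for ties.

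With n = 10 and k = 4, 12/(10·4·5) = 0.06 and 3·10·5 = 150. Let all 10 children follow the same pattern.

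- *Full retention* (medians 2, 3, 5, 5). Ranks within child are 1, 2, 3.5, 3.5 and rank sums 10, 20, 35, 35. ΣR² = 100 + 400 + 1225 + 1225 = 2950. Numerator: 0.06·2950 − 150 = 27. Each child has one tied pair (2³ − 2 = 6), so C = 1 − 60/600 = 0.9. χ² = 27/0.9 = 30.0.
- *Full loss* (medians 2, 3, 5, 2). Ranks are 1.5, 3, 4, 1.5 and rank sums 15, 30, 40, 15. ΣR² = 225 + 900 + 1600 + 225 = 2950. C is again 0.9 and χ² = 30.0.
- *Continued gain* (medians 2, 3, 4, 5). Rank sums are 10, 20, 30, 40 and ΣR² = 3000. χ² = 0.06·3000 − 150 = 30.0. Swapping weeks 12 and 16, or making week 16 the lowest visit, only permutes the rank sums, so it is again 30.0.

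The critical value on 3 df is 7.815. All five patterns give the same result. That relabelling visits leaves the statistic unchanged holds for any data.

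**Step 2: noisy data.** Simulation with 10 children, ALP means 3, 3.5, 4 at weeks 4, 8, 12, between-child SD 1.2, within-child SD 0.8, scores rounded to 1–8, no missed visits, 2,000 trials per setting. Ranges are across repeat runs.

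| Week-16 mean | Friedman p < 0.05 | Paired week 12 vs 16 Wilcoxon p < 0.05 |
|---|---|---|
| 4 (fully retained) | 58–61% | about 2% |
| 3 (fully lost) | 57–60% | 50–51% |
| 3.5 (half the gain lost) | not computed | about 12.5–14% |

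With stronger assumed learning (means 2, 3, 4, then 4, 2 or 3 at week 16; between-child SD 1.0, within-child SD 0.8; 1,000 trials), the Friedman test is significant in 99.7% (retained), 99.8% (lost) and 97.7% (half lost). With a flat profile it is significant in 4.0%.

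**Step 3: what the descriptive statistics would show.** In the constructed data the medians at weeks 12 and 16 go from 5 to 5 under retention and from 5 to 2 under loss. In the first simulation the mean falls by more than 0.5 point from week 12 to week 16 in 88% of full-loss trials and 8% of full-retention trials. The collected data therefore hold the information that the test leaves out.

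**The case against.** The strongest reply is that the p-value is not the only planned output. Section 2.9 promises central tendency, variability and 95% confidence intervals, and ALP levels at weeks 12 and 16 set side by side would usually reveal a large loss. The aim is only preliminary retention in a 10-child case series, feasibility results are to be presented qualitatively, and no stated decision hangs on a retention test. All of this stands and lowers the weight of the point. It does not make the named test suited to the question: no paired change from week 12 to week 16 is specified, so the retention reading stays informal.

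Three stronger readings are tempting, but the documents do not support them.

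- *That the follow-up cannot serve its aim.* It can, descriptively. Only the named inferential test fails to address it.
- *That the loss of children with a missed visit is a separate fault.* The standard Friedman test does need all four visits. At an assumed 10% of visits missed independently, 10·0.9⁴ = 6.6 children remain, against 10·0.9² = 8.1 for a two-visit comparison; at 20%, 4.1 against 6.4. But the article gives no missed-visit rate, the effect is nil if no visit is missed, and handling of missing data is commonly left to a fuller document that is not shown.
- *That the PFQ has the same problem.* It is a parent questionnaire on satisfaction, use, comfort and need for help. Learning and retention of skill do not apply to it.

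Nor should the paired test replace the Friedman test. In the first simulation a week 4 against week 12 contrast is significant in about 50% of trials, against about 61% for the omnibus test. The paired week 12 to week 16 test also misses full loss about half the time.

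**Conclusion.** The point holds for the ALP, as a minor one. The test that section 2.9 assigns to it gives practically the same rejection rate whether skill is kept or lost at week 16, so it does not address the retention aim in section 2.1. The planned descriptive statistics can do so only informally. The order-blindness is a mathematical property and needs no assumption. The percentages depend on the assumed means and SDs, and the routing to the Friedman test depends on reading the ALP phase as a numerical score.

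**What to change.** In section 2.9, keep the Friedman test and add one prespecified contrast for the ALP: week 16 minus week 12, on every child with both visits. Report mainly the median paired change with a 95% interval and a plot of each child's trajectory. Give the Wilcoxon p-value as secondary, and state that a non-significant result is not evidence of retention. Read the change next to the driving minutes in the follow-up journal, because driving that continues after week 12 is practice and not pure retention.

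The cost is two or three sentences and one extra comparison, with no new data collection. The estimate will be imprecise. With 10 pairs, an exact order-statistic interval for the median runs from the second-smallest to the second-largest change (coverage 1 − 2·(1 + 10)/1024 = 97.9%, ignoring ties), so it spans most of the observed changes.
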